### Serious adverse events

The following AEs will be considered to be serious AEs (SAEs): AEs that lead to death or life-threatening AEs, AEs requiring re-hospitalization for treatment or extension of the hospitalization period, AEs leading to persistent or marked disability or dysfunction, AEs that have the potential to cause birth defects in offspring, and AEs requiring treatment to prevent the above results, even if they do not result in immediate life-threatening events, death, or hospitalization.

The reporting procedure is as follows: If investigators are aware of the occurrence of SAEs, required reporting measures will be taken by the investigators, such as providing explanations to the enrolled patients and reporting to the principal investigator in accordance with the “standard procedure manual for handling serious adverse events in medical research for humans (Kyushu University)” and in compliance with the “Ethical Guidelines for Medical and Health Research Involving Human Subjects (Japan).” If a principal investigator is aware of the occurrence of SAEs, the principal investigator will also prepare an SAE report and submit it to the hospital director. The hospital director will then submit the report to the clinical trial ethics review committee. In addition, information regarding the occurrence of SAEs will be promptly shared with all investigators. The entire study will be discontinued if the clinical trial ethics review board deems it necessary.

### Statistics

#### Hypotheses and data analysis

The primary efficacy endpoint is the procedure time of the ESD. The null hypothesis is that the procedure time for the H-ESD and C-ESD procedures in patients with EGN is the same.

Analysis of the primary and secondary outcomes will be conducted using the FAS. We plan to analyze complete cases without imputation of missing data because this trial is designed to generate little missing data.

An analysis of covariance for the logarithmically converted ESD procedure time will be conducted with tumor location (upper or middle third of the stomach vs. lower third of the stomach), tumor size (0–9 mm vs. ≥10 mm), and operators’ experience with ESD (0–29 cases vs. ≥30 cases) as covariates. H-ESD will be considered a superior treatment procedure, compared with C-ESD, if the procedure time for H-ESD is significantly shorter than that for C-ESD. A 2-sided *p*-value <0.05 will be considered to indicate statistical significance. In the sub-analysis, if a subgroup factor is one of the covariates, the analysis will be performed without including the sub-group factor as a covariate.

Statistical analyses will be performed by independent statisticians at the Data Center of the Center for Clinical and Translational Research (CCTR) at Kyushu University Hospital. The data will be transferred to SAS statistical software version 9.4 (SAS Institute INC., Cary, NC, USA) for all analyses.

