### Population

#### Inclusion criteria

The inclusion criteria are as follows: (i) age ≥20 years of any sex; (ii) presence of EGN and capable of undergoing ESD as a local treatment; (iii) lesions diagnosed by endoscopic biopsy as gastric adenomas or adenocarcinomas; (iv) lesions endoscopically diagnosed as mucosal lesions ≤20 mm in diameter without ulceration ≤3 months prior to enrollment; (v) Eastern Cooperative Oncology Group Performance Status of 0–2; (vi) capable of listening to oral explanations and reading explanatory documents regarding doctors’ instructions as well as signing consent forms (including the informed consent that will be obtained before enrollment in the trial); and (vi) willingness to comply with all study procedures and be available for the duration of the study.

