### Endoscopists and equipment

Each procedure will be performed at one of the nine institutions by one of the participating endoscopists; each endoscopist in this study has been licensed to practice medicine in Japan for at least 2 years and has performed ≥500 endoscopies. Endoscopists without experience in C-ESD or H-ESD will be required to undergo hands-on training using a pig model before becoming an operator in the study. Handover of the procedure to another operator will be allowed if experienced endoscopists consider the handover clinically desirable for reasons such as prolonged procedure time over 60 min, massive uncontrollable bleeding, or the occurrence of perforation during the procedure. Procedure handover will be done and recorded if the supervisor determines that it is necessary.

Upper gastrointestinal endoscopes (EG-450-RD5, Fujifilm, Tokyo, Japan; GIF-Q260J, Olympus, Tokyo, Japan) attached to a disposable hood (Elastic touch, Top, Tokyo Japan, or D-201-11804, Olympus) will be used in the ESD procedures. A Flush Knife (DK2620J, Fujifilm) or Dual Knife (KD-650, Olympus) will be used in the C-ESD procedure. A SOUTEN (ST1850-20, Kaneka Medix, Tokyo, Japan) will be used in the H-ESD procedure. The SOUTEN is a hybrid knife that combines a needle knife and a snare, where a needle tip is attached to the top of the snare. No regulation is required for the types of injection needles in this study. An electrosurgical unit (ICC200, VIO300, or VIO3, ERBE, Tubingen, Germany) will be used as a high-frequency generator. Sodium hyaluronate solution or sodium alginate solution will be used as a viscous solution for submucosal injections from the injection needle. Normal saline or glycerol will be used for submucosal injections using the endo-knives. Coagrasper (FD-410LR, Olympus), Coagrasper G (FD-412LR, Olympus), RAICHO (RC-1900, Kaneka Medix), RAICHO 2 (RC1550-2, Kaneka Medix), and Hemostat Y (H-S2518, Pentax, Japan) forceps will be used if bleeding cannot be controlled using the endo-knife.

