### Randomization

Investigators from the participating institutions will have 24-h access to a Web-based central randomization system that provides immediate and concealed allocation. Eligible patients will be centrally randomized (1:1) into either the H-ESD or C-ESD group using the Web-based computer program, the Universal Hospital Medical Information Network (UMIN) Internet Data and Information System for Clinical and Epidemiological research (INDICE)-Cloud version. Randomization will be performed using dynamic balancing, which uses the minimization method by tumor location (upper third or middle third of the stomach vs. lower third of the stomach), tumor size (0–9 mm vs. ≥10 mm), and operators’ experience with ESD (0–29 cases vs. ≥30 cases). Patients and investigators will not be blinded to the allocated treatment group, and a unique patient identification number will be entered into the system to ensure anonymity.

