#### Sample size estimation

In this study, to test the superiority of H-ESD over C-ESD, the sample size was estimated based on the primary endpoint (the logarithmically converted procedure time for ESD). According to a previous report comparing the treatment outcomes of C-ESD and H-ESD, the logarithmically converted procedure times (minutes, mean ± standard deviation (SD)) for C-ESD and H-ESD were 1.578 ± 0.225 and 1.244 ± 0.228, respectively [12]. Considering these results, we hypothesized that H-ESD would provide a 0.2 (37%) reduction in procedure time and estimated the SD of 0.3 conservatively. Based on these assumptions, a total of 74 participants is needed to reach a power of 80% for a *t*-test with a significance level of 0.05. To compensate for a 10% dropout rate, we aim to include 82 participants in the study.

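### The primary ANCOVA is valid but uses tumour size only as below or at least 10 mm; adding pre-randomisation size in mm is a cheap gain in precision

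*Protocol article*

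**What the plan says.** The section Hypotheses and data analysis sets the primary analysis: "An analysis of covariance for the logarithmically converted ESD procedure time will be conducted with tumor location" in two classes, followed by "tumor size (0–9 mm vs. ≥10 mm), and operators’ experience with ESD (0–29 cases vs. ≥30 cases) as covariates". All three covariates are binary. They are the minimisation factors at the same cut-points; the Randomization section describes "dynamic balancing, which uses the minimization method by tumor location", size and operator experience.

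The inclusion criteria admit "lesions endoscopically diagnosed as mucosal lesions ≤20 mm in diameter without ulceration", so the upper size class runs from 10 to 20 mm. Under Definitions, tumour size is among the factors whose association with procedure time will be investigated, and dissection speed is resected area divided by dissection time.

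The sample size section states that "we hypothesized that H-ESD would provide a 0.2 (37%) reduction in procedure time and estimated the SD of 0.3 conservatively", and that "a total of 74 participants is needed to reach a power of 80% for a *t*-test with a significance level of 0.05". Enrolment is 82, to allow for 10% dropout.

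**The concern.** The protocol itself expects procedure time to depend on lesion size, yet the primary model keeps only one cut of that information. Two losses follow. Variation in time due to size differences within 0–9 mm or within 10–20 mm is counted as noise, which widens the interval for the treatment effect. And because minimisation uses the same cut, nothing balances or adjusts the arms for mean size within a class, where chance differences can arise in a trial of 82.

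The stake is precision, not validity. Precision matters because the planned effect may be optimistic. The Discussion reports a second retrospective study with a 23% reduction, which is −log10(0.77) = 0.114 on the log scale against the planned 0.2. With SD 0.3 and 37 per arm, power at 0.114 is about 36% if the covariates explain nothing.

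**Working it through.** **Inputs from the Protocol article.** Difference 0.2 on the log10 scale (1 − 10^−0.2 = 37%), SD 0.3, two-sided 0.05, 1:1 allocation, 74 evaluable patients (37 per arm).

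**Assumed, because the documents do not give them.** R², the share of within-arm variance of log time that is linear in size in mm: 0.05 to 0.30. The size distribution on 3–20 mm: three shapes.

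**1. The plan's own figure.** Two-sample t-test, noncentral t, with noncentrality 0.2 / (0.3 × √(2/37)): power is 80.8% at 37 per arm, so 74 reproduces. Adding 10% gives 74 × 1.1 = 81.4, hence 82. The planned ANCOVA has five coefficients (intercept, arm, three covariates) and so 74 − 5 = 69 residual degrees of freedom. If its covariates explain nothing, power is still 80.7%.

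**2. What the 10 mm cut keeps.** Let k be the squared correlation between size in mm and the indicator for 10 mm or more.

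| Assumed size distribution, 3–20 mm | Share at 10 mm or more | k |
|---|---|---|
| Uniform | 59% | 0.73 |
| Normal, mean 12, SD 4.5, truncated | 68% | 0.63 |
| Normal, mean 14, SD 4, truncated | 83% | 0.50 |

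The textbook value for a median split of a normal variable, 2/π = 0.637, lies inside this range.

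**3. Power.** Residual SD is 0.3 × √(1 − kR²) with the two-level term and 0.3 × √(1 − R²) with mm. Power uses 37 per arm and 69 degrees of freedom. The patient equivalent is 74 × [(1 − 0.637R²)/(1 − R²) − 1].

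| R² (assumed) | Two-level size, k 0.50–0.73 | Size in mm | Gain, points | Variance ratio, mm to two-level | Evaluable patients, k = 0.637 |
|---|---|---|---|---|---|
| 0.05 | 81.7–82.1% | 82.7% | 0.6–1.0 | 0.97–0.99 | 1.4 |
| 0.10 | 82.7–83.5% | 84.6% | 1.1–1.9 | 0.95–0.97 | 3.0 |
| 0.20 | 84.6–86.4% | 88.5% | 2.1–3.9 | 0.89–0.94 | 6.7 |
| 0.30 | 86.6–89.2% | 92.2% | 3.0–5.6 | 0.82–0.90 | 11.5 |

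Example: for R² = 0.20 and k = 0.637 the patient equivalent is 74 × (0.8726/0.80 − 1) = 6.7. Keeping the two-level term beside mm leaves 68 degrees of freedom and does not change these figures visibly (88.5% at R² = 0.20).

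**4. Simulation check.** 74 patients, uniform sizes, no centre variance, 4,000 replicates. Power went from 82.4% to 83.2% at R² = 0.10 and from 87.2% to 90.0% at R² = 0.25. The mean standard error went from 0.0678 to 0.0669 and from 0.0638 to 0.0611.

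**5. At the smaller effect of 0.114.** With k = 0.637, power goes from 40% to 43% at R² = 0.20 and from 43% to 48% at R² = 0.30.

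**The case against.** The strongest reply is that nothing here is wrong. The model adjusts for exactly the minimisation factors in their minimisation form, type I error is not threatened, and chance imbalance within a class is ordinary sampling error already in the standard error. The trial was sized on an unadjusted t-test with an SD of 0.3, above the 0.225 and 0.228 of the cited report, so the 80% target does not depend on how size enters. All of that stands, and it makes this an improvement rather than a correction.

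Three further limits also stand. The gain depends on an R² that the documents do not give, and it is small if R² is low. Linearity of log time in mm is assumed. The article does not say that the pre-randomisation mm value is stored: eligibility at 20 mm and minimisation at 10 mm imply a measurement, but the only mm measurements it spells out are the axes of the resected specimen, taken after randomisation.

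A reader might infer more in two directions.

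- **A fourfold area between 10 and 20 mm, (20/10)² = 4.** That is lesion area. Under Endoscopic procedures, marks lie 2–3 mm outside the margin and the incision lies outside the marks. Resected diameters are then at least 14–16 mm against 24–26 mm, an area ratio of at most (24/14)² = 2.9 or (26/16)² = 2.6. Procedure time also includes the circumferential incision, and H-ESD dissects only part of the area before snaring.
- **Leaving out institution is an equal loss.** It is true that "Each procedure will be performed at one of the nine institutions by one of the participating endoscopists" and that institution is neither a minimisation factor nor a covariate. But the documents give no between-centre variance and do not say that equipment differs by centre, and operator experience is already in the model. In simulation with nine unequal centres, size R² of 0.10 and the two-level size term, power with centre omitted, as fixed effects, or as a random intercept was 82.7, 78.0 and 82.7% at an ICC of 0; 82.8, 81.6 and 84.3% at 0.10; and 83.3, 85.8 and 87.8% at 0.20. The random-intercept figures treat the ICC as known and are therefore optimistic. Fixed effects lose power at low ICC, and a variance estimated from nine centres averaging 74/9, about 8 patients, is unstable.

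**Conclusion.** The point holds for tumour size, as a low-cost improvement to a valid primary analysis that meets its planned power. Using mm in place of the single cut gains about 0.6 to 6 power points at the planned effect for an assumed R² of 0.05 to 0.30, and lowers the variance of the treatment effect by about 1 to 18%. These ranges rest on the assumed R², on the three assumed size distributions, on rough linearity, and on reading the SD of 0.3 as the within-arm SD before adjustment.

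The documents do not support calling the model an error, a contradiction or a source of bias, nor claiming that omitting institution gives away precision. An institution term is a matter of judgement here.

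**What to change.** In Hypotheses and data analysis, before outcome data are seen, add tumour size in mm as a continuous covariate, beside or in place of the two-level size term. Specify it as the endoscopic size recorded before randomisation, not the specimen measurement. Keep tumour location and operator experience as planned, and report the planned two-level ANCOVA as a supportive analysis. State also whether the mm term stays in the model for the tumour-size subgroups, since the plan drops a covariate when it is the subgroup factor.

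The cost is at most one degree of freedom, the linearity assumption, and a check that the mm value is in the database. No patient or procedure is added. Because the trial is open-label and recruiting, the change should be a dated amendment. A random intercept for institution is at most an optional sensitivity analysis.

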#### Sample size estimation

In this study, to test the superiority of H-ESD over C-ESD, the sample size was estimated based on the primary endpoint (the logarithmically converted procedure time for ESD). According to a previous report comparing the treatment outcomes of C-ESD and H-ESD, the logarithmically converted procedure times (minutes, mean ± standard deviation (SD)) for C-ESD and H-ESD were 1.578 ± 0.225 and 1.244 ± 0.228, respectively [12]. Considering these results, we hypothesized that H-ESD would provide a 0.2 (37%) reduction in procedure time and estimated the SD of 0.3 conservatively. Based on these assumptions, a total of 74 participants is needed to reach a power of 80% for a *t*-test with a significance level of 0.05. To compensate for a 10% dropout rate, we aim to include 82 participants in the study.

#### Interim analyses

Interim analyses will not be performed. Considering the high curability and safety of H-ESD and C-ESD reported in the precious studies, patients would not be seriously disadvantaged by completing the study without an interim analysis.

### Data registration, handling, and retention

The trial database will be created by investigators entering anonymized data into the Web-based UMIN INDICE cloud. The trial data entry system and database will be secured and password-protected. The data management team and endpoint adjudication committee will be established by the principal investigator and independent statisticians at the Data Center of the CCTR at Kyushu University Hospital. Their responsibilities include the establishment of data randomization systems, electronic database report form design, data analysis, and verification. The principal investigator will retrieve the trial database after results from the last registered cases have been entered and submit it for final statistical analysis. Members of the data management team and endpoint adjudication committee will not participate in any intervention.

## Discussion

We expect that H-ESD will reduce the ESD procedure time for EGN compared with C-ESD. However, the results of two previous retrospective studies comparing the treatment outcomes of H-ESD and C-ESD are controversial. One of the reports regarding a multi-center study using a propensity score matching analysis showed a 53% reduction in procedure time for H-ESD, compared to that for C-ESD [12]. There were important limitations to this study, however, such as its retrospective nature and the use of a relatively small sample size (29 pairs after matching); furthermore, it was conducted using a propensity score matching analysis, and so there might be a confounding bias other than the factors involving matching. In contrast, another study conducted at a single center failed to demonstrate a significant difference in procedure time between H-ESD and C-ESD, although a 23% reduction was achieved using H-ESD [13]. This study was also performed retrospectively and with a small sample size (12 for C-ESD and 26 for H-ESD), both of which are important limitations. Although it was shown in this study that there were no significant differences in background characteristics of the enrolled patients between the two groups, it is not clear whether the small sample size might have affected the statistical analysis and/or the treatment outcomes. These findings further highlight the need for a multi-center RCT to confirm the benefits of H-ESD for EGN in clinical practice. Therefore, in this study, we will obtain an appropriate sample size and statistically calculate the results to further demonstrate the superiority of the H-ESD procedure time compared to that of C-ESD. Moreover, in this study, patients with EGN only who meet the “absolute indication of EMR or ESD” will be included based on the predetermined inclusion criteria, since 83% of enrolled patients met “the absolute indication” in our previous study showing the superiority of H-ESD over C-ESD [12].

The conventional EMR technique using snaring, on the other hand, has the limitation of curability. One of the disadvantages of EMR is that the en bloc resection rate is significantly lower than that of C-ESD, especially when the lesions are larger than 10 mm [8, 21, 22]. We expect that this limitation will be compensated for by H-ESD, where snaring is conducted after the circumferential incision and subsequent partial dissection. Therefore, the curability of each procedure will be set as a secondary outcome, and a sub-analysis will be performed on the data from lesions larger than 10 mm.

In the present clinical setting, lesions that fulfill the absolute indication for EMR or ESD are often performed by non-experts since ESD for these lesions is relatively easier than it is for other indicated lesions [5]. This study will, thus, include not only ESD experts but also non-experts, as operator endoscopists, to reflect real-world clinical practices, where the procedures conducted by non-experts are supervised by experts. We will then conduct a sub-analysis stratified by experts and non-experts, which will confirm its usefulness to both operators. Thus, we believe the results obtained from this study in this way will apply to clinical practice.

During the H-ESD procedure, we will use a multifunctional device (the SOUTEN high-frequency surgical knife) that will enable us to perform all procedures other than submucosal injection, including mucosal incision, submucosal dissection, and snaring, with a single device. Since performing ESD using the SOUTEN is much less expensive than it is with other conventional endo-knives, the SOUTEN may contribute to cost savings [19].

In this study, we aim to confirm the superiority of H-ESD over C-ESD for EGN. We expect that our findings will provide valuable information for determining the value of H-ESD for the standard treatment of EGN cases that fulfill the absolute indications for EMR or ESD.

## Trial status

This study was approved by the Kyushu University IRB for Clinical Trials (IRB No. 20202005) on July 28, 2020. This study was registered at UMIN-CRT (000041244) on July 29, 2020. Patients from Fukuoka or Oita prefecture in Japan are expected to participate in the trial. The trial was initiated at Kyushu University on August 1, 2020, and participation by other institutions will be allowed once IRB approval has been obtained from those institutions. Recruitment is expected to take 1 year and 8 months.

## Data Availability

Trial and data details can be obtained from the principal investigator upon reasonable request. The investigators plan to make data available through publication after completion of the study.

## Abbreviations

ER: Endoscopic resection
EGN: Early gastric neoplasms
EMR: Endoscopic mucosal resection
ESD: Endoscopic submucosal dissection
H-ESD: Hybrid ESD
C-ESD: Conventional ESD
CONSORT: Consolidated Standards of Reporting Trials
IRB: Institutional Review Board
TA-ESD: Traction-assisted ESD
RCT: Randomized controlled trial
UMIN: Universal Hospital Medical Information Network
INDICE: Internet Data and Information System for Clinical and Epidemiological research
AE: Adverse event
SAE: Severe AE
CCTR: Center for Clinical and Translational Research
